## 3.2. Source population

All first-trimester pregnant mothers of Jimma Zone within the age group of 15 – 49 years old during the study period will be the source population.

### 3.2.1*.* Study population

All first-trimester pregnant mothers of the selected clusters (kebeles) during the study period will be the study population.

### 3.2.2. Study Units

The selected study clusters will be the study unit. First-trimester pregnant mothers who will participate in the study will be a unit of analysis. Mothers who will participate in the study will be identified by doing home to a home census of the study clusters and fulfilling the criteria.

### 3.2.3. Inclusion criteria

All first-trimester pregnant mothers in the selected study area (cluster) who planned to give birth in the zone and are willing to give consent will be included.

### 3.2.4. Exclusion criteria

First-trimester pregnant mothers of the selected study clusters who have known (self-reported) chronic medical diseases (like diabetes mellitus, CHF, renal failure, epilepsy, HIV/AIDS) and temporary residents who will not stay in the study area until delivery. Mothers who are not willing to give consent for participation in the study and have multiple pregnancies after ultrasound scanning will be also excluded.

## 3.3. Study design

The study design will be a cluster-randomized controlled trial involving two arms. There will be intervention and control groups. The study clusters will be identified and arranged on the map first, by considering a buffer zone in between avoid information contamination. After all, the selected clusters will be assigned randomly either to the intervention or control groups ([See the map).](#_4.5._Sampling_procedures)

## 3.4. Sample Size Determinations

The sample size was estimated by G power version 3.1.9.7. Assumptions used to calculate the required sample size were: precision of 5%, power of 80%, an effect size of 0.25, and we expect a mean birth weight change of 100 gm (the primary outcome) in the intervention groups (from 2975 g to 3075 g) based on previous studies. Design effects of 2 and 15% non-response rates were also considered. The total sample size was 348 pregnant women (116 per each of the three study arms).

The sample size for each study cluster (kebele) will be allocated based on the proportion of their respective population. Accordingly, a total of eighteen clusters (kebeles) will be selected. From Mana and Seka districts eight and ten clusters (kebeles) respectively.

## 3.5. Sampling procedures

Two districts (woreda) that could represent the two known agroecological areas of the Jimma zone will be selected. Accordingly, Mana from predominantly coffee-growing districts and Seka Chekorsa from grain and crop-growing districts were selected purposively for management and logistical reasons. Then, non-adjacent clusters or kebeles (the smallest administrative units) will be selected from both districts to have buffer zones**.** Accordingly, a total of 18 clusters (8 from Mana and 10 from Seka chekorsa) districts will be selected. Using the randomized complete block design; the clusters (kebeles) will be grouped into two blocks based on their agroecological areas (mainly coffee or grain producing). Finally, from both blocks clusters will be randomly assigned to the three study arms (husband, Peers, and control). Thus, Nase, Bidaru toli, Dimtu (of Seka), Doyo toil, Gudata bula, and Lemi Lelisa clusters(kebeles) will be assigned to the husband group. While, Siba bake, Buyo kechema, Meti, Bore, Bebela kosa, and Haro clusters will be assigned to the peer group. Likewise, Komo hare, Gepa seden, Wakito madalu, Kamise waraba, kore Lelisa, and kenteri clusters will be assigned to the control group.

Regarding the sample size allocation, it was proportionally to the population size of respective districts and kebeles (clusters). A total of 348 first-trimester pregnant women will be enrolled at baseline, 144 women will be from the mana district (48 women in each arm), and 204 women will be from the Seka-chekorsa district (68 women in each arm). This means that a total of 116 1^st^ trimester pregnant women per the three study arms will be enrolled. All of the first-trimester pregnant women who will fulfill the inclusion criteria in each cluster will be enrolled until the desired or allocated number will be achieved.

[figure not shown]

Figure 2. Map of the study area with selected study clusters (kebeles) of both districts (Seka and Mana) source: Generated using ArcGIS software version 10.3 from ETHIO-GIS, 2014 database.

Jimma zone

21 Districts ( woredas)

Goma,

Limu kosa

Mana

Gera

Gumay

Limu seka

Boter –tolay

Chora- boter

Shebe- sombo

Non benja

Omo- Nada, Omo-Beyam

Sekachekorsa

Mancho

Dedo

Kersa

Tiroafata

Sokoru,

Santama

Sigimo

Gatira

Predominantly Grain/crops producing districts.

11 districts

---

Predominantly coffee growing districts,

10 districts

Mana district selected

Mana district

26 kebeles (clusters) total

Sekachekorsa district

37 kebeles (clusters) total

10 Clusters selected

8 Clusters selected

Coupled Intervention arm

3 clusters

Coupled intervention arm 3clusters

Mothers with their peers arm

4 clusters

Control arm

3clusters

Mothers with their peers arm

2 clusters

Control arm

3 clusters

Figure 3. Shows that the sampling procedure for the effect of home gardening and social behavioral change communication on feto-maternal outcomes in Jimma zone, South West Ethiopia, 2019.

Total=18 clusters

1. Husband intervention arm=6 clusters/kebeles (Nese, Gepa seden, Dimtu, Doyo toil, Gudata bula, Lemi lelise
2. Mothers with their peer intervention arm=6 clusters/kebeles (Siba beke, Meti,Buyo kechema, Bore,Babala kosa, Haro
3. Control arm = 6 clusters/kebeles (Bidaru tuli,Komo hare,Wakito medalu,Kemise waraba,Kore lelisa,Kenteri

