## 3.14. Statistical analysis

Data will be entered into Epi-data Version 3.1 for cleaning and sorting and then exported to SPSS version 20 for analysis. First, we will present descriptive information on the socio-demography of enrolled mothers, and then, baseline measurements will be compared between allocation groups by using mean difference or chi-squares. Comparison of the KAP scores, birth weight, hemoglobin level, and GWG, differences among the study arms will be done using ANOVA. The normality assumptions and the homogeneity of variance will be checked using a Q-Q plot and Levene’s test. The linear GEE regression analyses will be used to test the effects of the interventions on feto-maternal outcomes (birth weight and hemoglobin level) of difference in difference.

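### Clusters are randomised within two agro-ecological blocks, but the stated ANOVA and GEE name no block term, which can make a cluster-respecting test conservative and cost power

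*Protocol*

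**What the plan says.** Section 3.5 sets out the blocking: "Using the randomized complete block design; the clusters (kebeles) will be grouped into two blocks based on their agroecological areas". It then says that "from both blocks clusters will be randomly assigned to the three study arms (husband, Peers, and control"). The block sizes are uneven: "a total of 18 clusters (8 from Mana and 10 from Seka chekorsa) districts will be selected".

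Figure 3 gives the cluster counts. In the block of 10 the husband, peer and control arms have 3, 4 and 3 clusters. In the block of 8 they have 3, 2 and 3. The box labelled "Mothers with their peers arm" is the only one that differs between blocks. Overall the arms are equal at six clusters each, for example "Mothers with their peer intervention arm=6 clusters/kebeles".

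Section 3.5 also fixes how many women each district contributes. For Mana it says: "144 women will be from the mana district (48 women in each arm"). Seka Chekorsa is treated the same way, with a total of 204 split into 68 per arm.

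On analysis, section 3.14 plans an ANOVA across arms and states that "The linear GEE regression analyses will be used to test the effects of the interventions". The Abstract specifies a one-way ANOVA and a GEE. Neither place mentions block, district or agro-ecology as a model term, and section 3.6.2 does not list it among the independent variables. Section 3.14 does not name the GEE's cluster unit or working correlation.

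**The concern.** A trial that randomises within blocks would normally be analysed with those blocks in the model. The protocol treats agro-ecology as important enough to take one district from each zone and to randomise within them, and then names analyses that take no account of it.

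If the districts differ in mean birth weight, a model without block leaves that difference in the variation between clusters. The treatment contrast is largely protected from it by the blocking, but the estimated standard error is not. The reported error is then too large, the test rejects less often than its nominal level, and the precision that blocking was meant to buy is lost.

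A second question is whether the 4-and-2 split of peer clusters, against 3 and 3 in the other arms, lets a district difference into the peer-arm estimate.

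**Working it through.** **Inputs from the protocol.** 348 women, 116 per arm; 18 clusters laid out as in Figure 3; 48 women per arm in Mana and 68 in Seka Chekorsa; design effect 2; expected birth-weight difference 100 g.

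**Assumptions.** District difference D (not given), shown over a range. SD 450 g where grams are needed (not given). Equal cluster sizes within each arm and district. ICC from the protocol's own design effect: mean cluster size 348/18 = 19.33, so ICC = (2 − 1)/(19.33 − 1) = 0.0545.

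**1. Is arm confounded with district?**
- By women: the Mana share is 48/116 = 41.4% in every arm. A woman-level ANOVA or an independence GEE therefore has zero shift at any D.
- By clusters: the Mana share is 2/6 in the peer arm and 3/6 in the control arm. Equal-weight cluster means would shift peer minus control by (3/6 − 2/6) × D = 16.7 g per 100 g. The protocol plans no such analysis.
- Exchangeable GEE, with cluster weight m/(1 + (m − 1) × ICC):
  - Peer, Mana: 2 clusters of 24, 2 × 24/2.2545 = 21.29. Seka: 4 of 17, 4 × 17/1.8727 = 36.31. Mana share 21.29/57.60 = 37.0%.
  - Control, Mana: 3 clusters of 16, 3 × 16/1.8182 = 26.40. Seka: 3 of 22.67, 3 × 22.67/2.1818 = 31.17. Mana share 26.40/57.57 = 45.9%.
  - The shift is 8.9 g per 100 g of D. It is 2.8 g at ICC 0.01 and 11.5 g at ICC 0.10.

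**2. What omission does to the standard error.** In SD units, the variance of a cluster mean is 0.0545 + 0.9455/19.33 = 0.1034. Compare both intervention arms (12 clusters, 5 in Mana) with control (6 clusters, 3 in Mana). The district difference adds D² × (12 × 5/12 × 7/12 + 6 × 3/6 × 3/6)/16 = 0.276 D² to the residual mean square.
- D = 0.25: 0.1034 + 0.0173 = 0.1207. The reported error is inflated by √(0.1207/0.1034) = 1.08.
- D = 0.5: 0.1034 + 0.0690 = 0.1724. The inflation is √(0.1724/0.1034) = 1.29.

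**3. Power for a 0.5 SD effect, both intervention arms against control, by simulation on the Figure 3 layout.** Each cell is without block / with block. The GEE columns use 2,500 trials per setting and cluster-robust variance. The cluster-weighted columns use 20,000 trials and the weights in step 1.

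| District difference | Independence GEE | Cluster-weighted, Seka heavier | Cluster-weighted, Mana heavier |
|---|---|---|---|
| 0 | 82% / 82% | 83% / 82% | 83% / 82% |
| 0.25 SD | 79% / 82% | 79.8% / 82.1% | 76.5% / 82.4% |
| 0.5 SD | 64% / 82% | 69.2% / 82.7% | 59.7% / 82.5% |

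The loss is 2 to 3 points at 0.25 SD and about 13 at 0.5 SD where the small shift from step 1 helps (Seka heavier). It is about 6 and 23 where the shift works against the treatment effect (Mana heavier). Under independence, where there is no shift, it is 3 and 18.

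Type I error without block was 4.0% and 1.6% at 0.25 and 0.5 SD for the independence GEE, and about 3.6% and 1.5% for the cluster-weighted test. With block, the cluster-weighted test held 5%. The independence GEE with block rejected 5.6% to 6.4%, slightly over nominal with 18 clusters, so a little of its apparent gain is not real.

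**4. At the protocol's own 100 g, peer against control** (SD 450 g, cluster-weighted, 15% loss). Power with block is about 18 to 19% throughout. Without block it is 13.5% if Mana is 100 g heavier, 18% if Seka is 100 g heavier, and 7% and 12% at 200 g.

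**5. The woman-level ANOVA.** Omitting block adds D² × 0.414 × 0.586/SD² to the residual variance: 1.2% at 100 g and 4.8% at 200 g.

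**The case against.** A reader might infer that the uneven peer clusters bias the peer-arm estimate. As a general statement that does not stand: section 3.5 fixes 48 and 68 women per arm by district, so the shift is zero unless the analysis weights by cluster. Uneven loss to follow-up could reopen a small imbalance.

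A reader might also infer that the planned ANOVA is conservative. It is not, if run on individual women without regard to clustering. In simulation at this ICC with no treatment effect, its type I error was 21 to 23% whether the districts differed by 0 or 0.5 SD. That is a separate fault, which a block term does not repair.

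A third tempting reading is that the clusters should be redrawn as 9 + 9 or 6 + 12, since neither 8 nor 10 divides by three. But every arm appears in both blocks; only the replication is unequal. A redraw would disturb the population-proportional allocation, the non-adjacent clusters chosen for buffer zones, and the kebeles already named.

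Three further objections have force. The district difference is assumed, and 0.5 SD at an SD of 400 g would be 200 g, twice the expected effect. For haemoglobin analysed as a difference in differences, a constant district level cancels, so the point bears mainly on birth weight, which has no baseline. And a statistical analysis plan may add covariates to the GEE, so the firm statement is only that the analyses stated in the protocol name no block term. Even so, a one-way ANOVA by arm has no place for a block factor and would have to change to match the blocked randomisation.

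**Conclusion.** The point holds in limited form. The randomisation is blocked and the stated analyses do not reflect it. In an analysis that respects clustering, omission is harmless if the districts do not differ. Otherwise it makes the test conservative: for a 0.5 SD effect, about 2 to 3 power points are lost at a 0.25 SD district difference and about 13 at 0.5 SD, and more in a cluster-weighted analysis if Mana is the heavier district. These figures rest on ICC 0.0545, derived from the protocol's design effect, and on an assumed district difference. Any shift in the peer-arm estimate is conditional on cluster weighting and small, about 9 g per 100 g of district difference for an exchangeable GEE. This should be corrected, but it does not invalidate the design.

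**What to change.** In section 3.14, state that district (the randomisation block) enters the GEE comparison of arms as a fixed effect, above all for birth weight, and enters any ANOVA that is kept, which is then no longer one-way. Align the Abstract.

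The cost is one degree of freedom. In the cluster-weighted simulation, power at zero district difference changed by less than one point. With block in the model the shift in the peer-arm estimate also disappears under cluster weighting, so on this point the choice of working correlation no longer matters. No change to the cluster list is needed.

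### Section 3.5 and the list under Figure 3 assign two kebeles, Bidaru toli and Gepa seden, to opposite arms (husband and control)

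*Protocol*

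**What the plan says.** Section 3.5 describes random assignment of kebeles to three arms (husband, peer, control) within two agroecological blocks, and then names the result. For the husband arm: "Thus, Nase, Bidaru toli, Dimtu (of Seka), Doyo toil, Gudata bula, and Lemi Lelisa clusters(kebeles) will be assigned to the husband group". For control: "Komo hare, Gepa seden, Wakito madalu, Kamise waraba, kore Lelisa, and kenteri clusters will be assigned to the control group". For the peer arm: "Siba bake, Buyo kechema, Meti, Bore, Bebela kosa, and Haro clusters will be assigned to the peer group".

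The list under Figure 3 names the result again. For the husband arm: "Husband intervention arm=6 clusters/kebeles (Nese, Gepa seden, Dimtu, Doyo toil, Gudata bula, Lemi lelise". For control: "Control arm = 6 clusters/kebeles (Bidaru tuli,Komo hare,Wakito medalu,Kemise waraba,Kore lelisa,Kenteri".

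On numbers of women, section 3.5 gives for Mana "144 women will be from the mana district (48 women in each arm" (the quote stops before the closing bracket). For Seka Chekorsa the same section has 204 in total, which is 68 per arm. Section 3.4 gives the overall figure: "The total sample size was 348 pregnant women (116 per each of the three study arms". Both sections say that numbers per kebele follow population size, but no figure for any kebele is printed.

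**The concern.** A single randomisation has one result, and the protocol states two. Both lists are current text and neither belongs to a record of changes. The kebele is the unit that is randomised, so each entry decides the arm of every woman enrolled there.

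The conflict lies between the husband arm and control, not between the two intervention arms. On one list a kebele gets the education sessions, seeds and home visits of section 3.7; on the other it gets only routine antenatal education. The exchange is also reciprocal: both lists keep six clusters per arm, so a check of cluster totals would not find it. Anyone setting up delivery, or coding the arm variable for the ANOVA and GEE comparisons in section 3.14, has two sources that disagree.

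**Working it through.** **1. Name-by-name match.** Spelling variants and order are ignored.

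| Kebele | Arm in section 3.5 text | Arm in list under Figure 3 |
|---|---|---|
| Bidaru toli / tuli | husband | control |
| Gepa seden | control | husband |
| Nase / Nese, Dimtu, Doyo toil, Gudata bula, Lemi Lelisa / lelise | husband | husband |
| the six peer kebeles | peer | peer |
| Komo hare, Wakito madalu / medalu, Kamise / Kemise waraba, Kore Lelisa, Kenteri | control | control |

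Sixteen kebeles match and two do not. The names are distinctive and each occurs once per list, so this is not a matter of spelling.

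**2. The plan's own totals.** 3 × 48 = 144 for Mana; 3 × 68 = 204 for Seka Chekorsa; 144 + 204 = 348; 48 + 68 = 116 per arm. These reproduce sections 3.4 and 3.5.

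**3. Women in the two kebeles.** Figure 3 gives the husband and control arms three clusters each in both districts. With equal cluster sizes within a district arm (an assumption), women per cluster = women per district arm / 3.

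| Case | Women per cluster | Both kebeles | Share of 348 | Share of each affected arm (116) |
|---|---|---|---|---|
| Both in Mana | 48/3 = 16 | 32 | 9.2% | 13.8% |
| Overall cluster average | 348/18 = 19.3 | 38.7 | 11.1% | 16.7% |
| Both in Seka Chekorsa | 68/3 = 22.7 | 45.3 | 13.0% | 19.5% |

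The district is uncertain. In the husband list the words in brackets naming Seka follow Dimtu and may or may not cover the names before it. No place in the text gives a district for Gepa seden. If the two kebeles lay in different districts, the two lists could not both fit the three-and-three cluster counts in Figure 3, which would be a further inconsistency.

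**4. Conditional illustration of dilution.** Suppose delivery followed one list and the arm variable in the analysis followed the other. Let p be the share of each of the two arms that is mislabelled, and let D be the true husband-control difference, taken as the same in all clusters. The labelled husband mean is (1 − p) × husband + p × control, and the labelled control mean is the reverse. The observed difference is therefore (1 − 2p) × D. Section 3.4 plans on 100 g (2975 g to 3075 g).

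- p = 0.138: 1 − 0.276 = 0.724, so about 72 g
- p = 0.167: 1 − 0.333 = 0.667, so about 67 g
- p = 0.195: 1 − 0.391 = 0.609, so about 61 g

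**The case against.** The best case on the other side grants the contradiction and limits what may be built on it. All of the following stands.

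- A reader might infer that some women received, or were analysed under, the wrong treatment. The protocol does not show that. It states planned assignment twice and differently, and says nothing of what was delivered.
- A reader might infer that an allocation was changed after randomisation. One exchanged pair fits a transcription slip equally well, and the document supports neither reading over the other.
- A reader might take 45 women, 20% of an arm and 61 g as the size of the problem. They are only the upper end of the range in the working, and they need both kebeles to be in Seka and clusters to be equal in size. Because enrolment is proportional to population, the true count could fall outside 32 to 45.
- The dilution needs two teams to work from different lists. Nothing in the protocol suggests this, and the compliance counts in section 3.7.4 and Table 2 (attendance, seeds received, home visits) would tend to reveal it. If delivery and analysis use the same list there is no dilution, and the open question is only whether that list is the one drawn.
- Section 3.3 sends the reader to the map, and Figure 2 is not reproduced in the copy reviewed. It may show the arms. That could help to settle the matter, but the two printed lists would still conflict.

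None of this reconciles the lists.

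**Conclusion.** The concern holds as a contradiction in assigned arm for 2 of 18 randomised clusters, one of six in each of the husband and control arms. That statement rests on the two lists alone and needs no assumption.

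The size in women is an estimate: about 32 to 45 of 348, or about 14 to 20% of each of the two arms, given equal cluster sizes within a district arm and both kebeles in one district. The 61 to 72 g range is an illustration of what crossing the lists would do, not a predicted bias. The documents do not show which list is right or why they differ.

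It should be corrected before either list is relied on, because it concerns the allocation of the randomised unit across the line between intervention and control.

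**What to change.** Retrieve the original random-assignment record. Replace both lists with one allocation table that gives kebele, district or block, and arm for all 18 clusters, with one spelling of each name, and bring Figure 3 and the map into line with it. Name that table as the sole source of arm for both delivery and analysis.

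If the record shows that an allocation was changed after randomisation, analyse by the arm originally drawn and report the change with its reason. If it shows a transcription error, correcting the wrong list is enough.

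The cost is one check of the record and a one-table correction. Sample size, visits and measurements are unaffected.

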## 3.6. Study Variables

### 3.6.1. Dependent variables

- Birth weight
- Minimum dietary diversity scores
- Wasting (MUAC) and anemia
- Gestational Weight gain
- Nutritional Knowledge, attitude, and practice

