## Research hypothesis

1. Pregnant women who are involved in nutrition education and home gardening interventions will have a better dietary diversity score and nutritional status than the controls.
2. Pregnant women who are involved in nutrition education and home gardening interventions will give more normal birthweight neonates than the controls.

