## 2.2. Specific objective

- 1. To measure the effect of nutritional education and home gardening interventions on minimum dietary diversity scores among pregnant women of Jimma zone.
  2. To determine the effect of nutritional education and home gardening interventions on the nutritional status among pregnant women of Jimma Zone.
  3. To determine the effect of nutritional education and home gardening interventions during pregnancy on fetal birth weight in Jimma zone.

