## 3.12. Anthropometric measurements

The pregnant mothers will be weighed at the begging and last ANC follow-up without shoes and with minimal or light clothing using a Seca digital scale. The readings will be taken to the nearest 0.1kg. It will be calibrated against known weight regularly. MUAC will be measured during the enrolment and at the end of the follow-up to assess wasting among the study subjects using an adult MUAC non-stretchable measuring tape to the nearest 0.1 cm. The Mid-upper arm circumference will be measured midway between the lateral projection of the acromion process of the scapula and the inferior margin of the olecranon process of the ulna.

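### MUAC is a listed outcome measured twice, but the analysis section names no end-line or change comparison of it, so objective 2 would rest on hemoglobin and gestational weight gain

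*Protocol*

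**What the plan says.** Section 2.2 sets as its second specific objective "To determine the effect of nutritional education and home gardening interventions on the nutritional status among pregnant women of Jimma Zone". The first research hypothesis states that women receiving the interventions "will have a better dietary diversity score and nutritional status than the controls". Neither names a measure of nutritional status.

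Section 3.6.1 lists the dependent variables. One item is "Wasting (MUAC) and anemia"; "Gestational Weight gain" is a separate item.

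Section 3.12 states that "MUAC will be measured during the enrolment and at the end of the follow-up to assess wasting among the study subjects". Section 3.8 includes MUAC and hemoglobin in the baseline data, and section 3.13 measures hemoglobin at baseline and end line.

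Section 3.14 has three comparisons between arms. Baseline measurements are compared by mean difference or chi-square. KAP scores, birth weight, hemoglobin level and gestational weight gain are compared by ANOVA. Linear GEE models in difference-in-difference form are used "to test the effects of the interventions on feto-maternal outcomes (birth weight and hemoglobin level").

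**The concern.** The outcome list and the analysis section do not match. A measure that the protocol lists as an outcome, and takes twice for the stated purpose of assessing wasting, has no outcome comparison in the section that says what will be compared.

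The stake is what the trial may say about objective 2. Hemoglobin and gestational weight gain do not measure wasting. If the analysis follows section 3.14, a finding on hemoglobin could be reported as a finding on nutritional status while the trial's only wasting measure stays unexamined. If MUAC is analysed anyway, the choice of end-line value, change or adjusted value would be made without a plan, possibly after the data are seen.

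**Working it through.** **Step 1. Listed outcomes against named analyses.** The protocol gives no figure to reproduce here, so the check is an item-by-item match of section 3.6.1 against section 3.14.

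| Dependent variable (3.6.1) | Outcome comparison in 3.14 |
| --- | --- |
| Birth weight | ANOVA and linear GEE |
| Minimum dietary diversity score | none named |
| Wasting (MUAC) | none named |
| Anemia | hemoglobin level, by ANOVA and linear GEE |
| Gestational weight gain | ANOVA |
| Knowledge, attitude and practice | ANOVA |

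Two items have no outcome analysis: MUAC and dietary diversity. Anemia is covered through hemoglobin as a continuous measure. Enrolment MUAC does fall under the baseline comparison in 3.14, but that cannot show an intervention effect. End-line MUAC has no named use.

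**Step 2. Is MUAC tied to objective 2?** No sentence says so. The nearest link is section 1.1, which gives MUAC below 21 cm and anemia as examples of poor maternal nutritional status indicators. Taking both as measures behind objective 2 therefore follows the protocol's usage but remains an inference.

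**Step 3. What a MUAC analysis could detect (illustration).**

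Inputs from section 3.4: 348 women in three arms of 116, 15% non-response, design effect 2. Assumptions not in the protocol: a true shift of 0.3 SD in MUAC; a correlation r between enrolment and end-line MUAC of 0.6 to 0.8; equal loss across arms; the same design effect for MUAC.

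- Effective total: 348 × 0.85 / 2 = 147.9, which is 49.3 per arm, or 98.6 in the two intervention arms together.
- Pooled contrast (98.6 v 49.3): SE in SD units = √(1/98.6 + 1/49.3) = 0.174.
- Power ≈ Φ(0.3 / (SE × √v) − 1.96), two-sided 5%. The factor v is 1 for end-line values alone, 2(1 − r) for change scores and 1 − r² for baseline adjustment.

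| Analysis | r = 0.6 | r = 0.7 | r = 0.8 |
| --- | --- | --- | --- |
| End-line MUAC alone | 41% | 41% | 41% |
| Change score | 49% | 60% | 78% |
| End-line adjusted for enrolment value | 58% | 67% | 82% |

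Adjustment is never less precise than the change score, because 2(1 − r) − (1 − r²) = (1 − r)² ≥ 0.

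The protocol does not plan to pool the two intervention arms. For one intervention arm against control, SE = √(2/49.3) = 0.201. The adjusted analysis then gives about 46% at r = 0.6 (z = 0.3 / (0.201 × 0.8) = 1.86) and about 70% at r = 0.8 (z = 0.3 / (0.201 × 0.6) = 2.48).

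**The case against.** The strongest reply is that a separate statistical analysis plan may cover this. Birth weight is the primary outcome, MUAC is secondary, and section 3.14 does not call its list exhaustive. Models and cut-offs for secondary outcomes are often left to such a plan. For the cut-offs for wasting and anemia this stands, and their absence is not part of the point. It does not dispose of the rest: section 3.14 names specific outcomes for two methods and leaves out one that 3.6.1 lists and 3.12 measures for this purpose. That is a mismatch inside the protocol.

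Four stronger readings are tempting, and the document supports none of them.

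- A reader might infer that MUAC is never compared between arms. The baseline comparison in 3.14 takes in enrolment MUAC; only the outcome comparison is missing.
- A reader might infer that 3.6.1 defines nutritional status as wasting and anemia. It is a plain list of dependent variables and does not use the term. Gestational weight gain could also be read as an indicator, and it is tested.
- A reader might infer that testing hemoglobin level in place of anemia is an error. A continuous outcome uses more of the information, and 3.14 names only the level, so it leaves no choice open there.
- A reader might take the power figures as the trial's expected performance. They rest on an assumed shift, assumed correlations and, for 58-82%, a contrast the protocol does not plan.

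**Conclusion.** The point holds in a limited form. Section 3.14 names no end-line or change analysis of MUAC, although MUAC is a listed outcome measured at both ends of follow-up. As written, objective 2 would be answered by hemoglobin and gestational weight gain, with wasting untested.

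This rests on comparing sections 3.6.1, 3.12 and 3.14 and does not depend on the power figures, which show only that an adjusted MUAC analysis would be informative under plausible assumptions. The primary outcome is unaffected. One of three specific objectives lacks a named measure and leaves a listed indicator without a test, so the plan should be amended. The gap for dietary diversity is of the same kind and touches objective 1.

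**What to change.** 1. In section 3.14, add end-line MUAC in cm, as a continuous outcome, to the linear GEE clustered on kebele. Use arm on three levels (as in 3.4 and 3.5) as the effect, enrolment MUAC and district block as covariates, and a small-sample correction for the 18 clusters.
2. Analyse end-line hemoglobin the same way with its baseline value, and state that this replaces the difference-in-difference form for that outcome.
3. Align 2.2 and 3.6.1 so that nutritional status names MUAC and hemoglobin level. Percentages with wasting and anemia may be descriptive, with cut-offs left to the statistical analysis plan.
4. Name an outcome analysis for dietary diversity in 3.14 at the same time.

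The MUAC and hemoglobin changes use data already planned at both time points. They cost wording in three sections, one more secondary outcome compared across three arms, and a respecified hemoglobin model. The added comparisons should be reported as secondary.
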